### Criteria for discontinuing or modifying allocated interventions {11b}

During each TEE scan, the examination will be immediately halted if any adverse events resulted from TEE occur or have the potential to occur. If a sign of a rapid rescue emerges, the trial will also be halted, and the expert and anesthesiologists in charge will then take over instead.

### Strategies to improve adherence to interventions {11c}

The TEE operators and the expert will be comprehensively trained before the initiation of this trial. Further, chief anesthesiologists will be informed of the trial protocol aimed at being not allowed to interpret the trial.

### Relevant concomitant care permitted or prohibited during the trial {11d}

All patients included will receive standard anesthetic plan in the operating room and post-operative treatment in the intensive care unit and general ward.

### Provisions for post-trial care {30}

Eligible patients will receive at least two rounds of intraoperative TEE scans and treatment for TEE-associated complications for free.

### Outcomes {12}

#### Primary endpoint

The primary endpoint we define is the difference in terms of correctly discriminating causes in the phase of CPB separation within specified 120 s between the PReTEE group and the conventional TEE group. A correct diagnosis by TEE is defined as the extent of agreement up to 70% and greater between the conventional TEE/PReTEE and the expert TEE; otherwise, an uncorrected diagnosis would be accounted for.

#### Secondary endpoints

This trial has eight secondary endpoints to be further assessed, which are listed as follows:Detection rate of hypovolemiaHypovolemia is defined as a small left ventricular cavity size associated with normal or hyperdynamic global left ventricular systolic function.Detection rate of outflow tract obstructionThe obstruction we will observe includes pulmonary embolism or left ventricular outflow tract obstruction. For pulmonary embolism, thrombus mass visualized in the pulmonary artery, right atrium/ventricular is a direct indication but relatively rare; Indirect sign from TEE finding may be concluded as a dilated right atrium/ventricle with right ventricular akinesia. Left ventricular outflow tract obstruction is the occurrence of systolic anterior motion of the mitral valve accompanied by mitral regurgitation or not.Detection rate of regional wall motion abnormalityDetection rate of left ventricular systolic dysfunctionDysfunction will be assessed via direct eyeballing with an indication of reduced or absent left ventricular systolic wall motion and systolic wall thickening. Grades of dysfunction (mild, moderate, and severe) will also be subsequently estimated.Detection rate of right ventricular systolic dysfunctionRight ventricular enlargement, severely decreased or absent right ventricular free wall endocardial excursion or wall thickening, or a D-shaped left ventricular cavity were all indications of right ventricular dysfunction.Detection of decreased peripheral vascular resistanceDetection of valvular abnormalitiesDetailed information of valvulopathy in terms of valve categories and corresponding lesions will be additionally recorded.The incidence of TEE-associated complicationsMajor complications caused by intraoperative TEE probe insertion, manipulation and rotation include gastrointestinal bleeding or tearing or perforation. Moreover, the minor complications we will identify include lip or dental injuries, oral trauma/bleeding, odynophagia, and swallowing dysfunction.

## Safety evaluation

Safety evaluation accounted for in the study is composed of any TEE-linked adverse consequences, like esophageal perforations, pharyngeal trauma, and gastrointestinal bleed.

### Participant timeline {13}

Table 2 depicts the timeline designed for our trial.

**Table 2 Tab2:** Participant timeline

Participate timeline
Electronic medical system
Eligibility screening
General cardiac ward
Written informed consent
A collection of baseline characteristics
Surgery
Intervention: The PReTEE group, the conventional group
The diagnosis efficiency regarding leading causes of difficult CPB separation
TEE-associated adverse complications Surgical data

### Sample size {14}

In our preliminary experiment, the time of finding out the cardiac etiologies in the PReTEE group was 36 s, whereas in the conventional group was 100 s. The preliminary results have never been published. Twenty PReTEE exams were performed using the available simulator employed at our center. Considering the apparent reduction of timing of diagnosis, no further PReTEE exams are planned to be conducted in cardiac surgical patients. However, one TEE scanning procedure in the conventional group was implemented for one cardiac patient in the operating room. To achieve a 90% power at a significance level of 5%, 42 TEE examinations should be conducted among eligible patients using a hazard ratio of 2.78. Considering a 20% dropout rate, a total of 46 TEEs are schemed to be consecutively performed. The sample size calculation was achieved using the gsDesign package via R software.

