### Intervention description {11a}

General cardiac anesthesia induction and maintenance will be prescribed at the chief anesthesiologist’s discretion. CPB procedure at our institute complies with a standardized pattern. The separation of CPB is ended with the administration of protamine and the removal of the venous and arterial cannulas. All patients during intraoperative periods will receive a round of TEE examination before and after CPB routinely. Hemodynamic parameters and TEE findings are two major determinants in the process of CPB separation. Following the completion of surgical procedures, patients will be admitted to the intensive care unit for further advanced monitoring and therapy. The timing of transfer from intensive care unit to the general ward will depend on patient physical recovery status.

When the process of CPB separation initiated, the TEE probe is immediately inserted by the TEE operators. Then they are required to remove and rotate the probe and to promptly detect the leading causes of complex CPB separation. After the probe is well inserted, the time taken in seconds till TEE scan completion will be measured by the study recorder. The etiology interpretations and their corresponding TEE views will also be reported to the recorder by operators and simultaneously kept in a form of questionnaire (Supplemental file 1). The maximum time for TEE sequence scanning permitted is 120 s. The number of both junior TEE operators and eligible patients available at our institute are to some extent of limitation; therefore, TEE examination for each patient is not conducted by equal numbers of operators stratified by allocation groups. During patient examinations by operators and the expert, the TEE probe is kept still.

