## Statistical methods

### Statistical methods for primary and secondary outcomes {20a}

The R software will be ultimately employed to perform all statistical analysis. The continuous data will be summarized as median (standard deviation) or median (interquartile range), whereas categorical data as number (percentage). Based on the time to event in the process of estimating the difference regarding diagnostic efficiency between the conventional TEE group and the PRe TEE group, a Cox proportional hazards model will be considered. In the Cox model, we will treat the TEE operators who failed the diagnosis as censored. A *P* < 0.05 will be considered statistically significant.

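### The sample size treats all 42 scans as events and under-allows for dropout, so 46 scans do not give the stated 90% power at a hazard ratio of 2.78

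*Protocol article*

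**What the plan says.** The section Sample size {14} gives pilot results: "the time of finding out the cardiac etiologies in the PReTEE group was 36 s, whereas in the conventional group was 100 s". On their origin it says "Twenty PReTEE exams were performed using the available simulator employed at our center", and that "one TEE scanning procedure in the conventional group was implemented for one cardiac patient in the operating room". It then concludes that, for 90% power at 5%, "42 TEE examinations should be conducted among eligible patients using a hazard ratio of 2.78", and sets the total at 46 to cover a 20% dropout. The calculation is attributed to the R package gsDesign, without the function or its settings.

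Three other statements decide how many of those scans can count as events:

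- Intervention description {11a}: "The maximum time for TEE sequence scanning permitted is 120 s".
- The same section defines success as the correct cause within that limit. An absent or wrong diagnosis is a failure.
- Statistical methods {20a}: in the Cox model "we will treat the TEE operators who failed the diagnosis as censored".

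**The concern.** Power in a Cox analysis comes from events, and here an event is a correct diagnosis within 120 s. The sample size paragraph counts examinations and mentions no event probability. If 42 examinations are to carry the information of about 41 events, practically no operator may fail in either arm. That sits badly with a primary endpoint defined as a between-group difference in correct discrimination within 120 s, since such a difference exists only if some scans fail.

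The step from 42 to 46 also does not match a 20% loss. Finally, the effect size is a ratio of two pilot times that appear to come from different settings.

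What is at stake is how the result is read. A non-significant finding would be presented as coming from a trial with 90% power when the plan's own inputs give less.

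**Working it through.** **Inputs.** From Sample size {14}: hazard ratio (HR) 2.78, power 90%, level 5%, 46 scans, 20% dropout, pilot times 36 s and 100 s. From Intervention description {11a}: cap of 120 s. From Statistical methods {20a}: failures censored. My assumptions: a two-sided test (the protocol says only "A *P* < 0.05 will be considered statistically significant"), equal numbers of scans per arm (the 1:1 ratio is stated for operators) and, in step 4, exponential times.

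**1. Reproducing 42.** Schoenfeld's formula with equal arms:

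d = 4(z₀.₉₇₅ + z₀.₉₀)² / (ln HR)² = 4(1.960 + 1.282)² / (ln 2.78)² = 40.2

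That is 41 events, or 42 as an even total. Other routes:

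| Method | Two-sided 5% | One-sided 5% |
|---|---|---|
| Schoenfeld (events) | 41 | 33 |
| Freedman (events) | 48 | 39 |
| Lachin–Foulkes, hazard difference, no censoring (scans) | 51.5 | 42.3 |
| Lachin–Foulkes, hazard difference, 120 s cap (scans) | 57–63 | 47–52 |

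The two routes that land near 42 are two-sided Schoenfeld and one-sided Lachin–Foulkes without a cap. Both leave no room for censoring once 42 is read as a number of scans.

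**2. Dropout.** 42/0.8 = 52.5, so 53 scans. Multiplying instead, 42 × 1.2 = 50.4, so 51. The planned 46 allows 1 − 42/46 = 8.7% loss.

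**3. Ceiling after the stated loss.** 46 × 0.8 = 36.8 scans, already fewer than 41. If every one were an event:

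Power = Φ(√(d/4) × ln HR − 1.96) = Φ(√9.2 × 1.0225 − 1.96) = Φ(1.14) = 87%

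This step needs no assumption about the shape of the times.

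**4. Effect of the 120 s cap at HR 2.78.** The protocol does not say whether 36 s and 100 s are means or medians, so both are shown.

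- Medians: P(event by 120 s) = 1 − 2^(−120/36) = 0.90 and 1 − 2^(−120/100) = 0.56; average 0.73.
- Means: 1 − e^(−120/36) = 0.96 and 1 − e^(−120/100) = 0.70; average 0.83.

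| Scans analysed | Events (medians) | Power | Events (means) | Power |
|---|---|---|---|---|
| 46, no dropout | 33.7 | 84.3% | 38.3 | 88.5% |
| 36.8, after 20% loss | 27.0 | 75.6% | 30.6 | 80.7% |

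Log-rank simulation with 23 scans per arm and the cap gives 85% (medians) and 88% (means), in line with the formula. These figures take every diagnosis made in time as correct. If 10% of them were wrong (an assumed figure), power would be 80–85% without dropout and 71–77% with it. Clustering of scans within the six randomised operators is not modelled.

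**5. The hazard ratio.** 100/36 = 2.78. A ratio of mean or median times equals a hazard ratio only for exponential times. The choice matters: 42 events give 84% power at HR 2.5 and 61% at HR 2.0.

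**The case against.** Four points can be made for the plan.

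*The shortfall depends on exponential times.* A reader might infer that 90% is unattainable under the pilot times whatever their distribution. The documents do not support that, because no spread or distribution is given. If 36 s and 100 s are kept but times vary less than exponential, the implied HR is larger. With Weibull shape 1.25 it is 2.78^1.25, about 3.6, and simulated power with the cap is 97–98% for 46 scans and 91–94% for 36. This stands, so the claim must be tied to HR 2.78, the value the protocol itself plans on. With the HR held there, simulated power stays near 84–88% for 46 scans and 75–80% for 36 across the shapes tried.

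*The calculation cannot be identified.* It is tempting to say that 42 simply is an event count mislabelled as scans. The gsDesign call and the sidedness are not printed, and the one-sided Lachin–Foulkes figure is a count of subjects. What can be said is that neither route allows for censoring. Sidedness also matters to the size: a one-sided 5% test needs 33 events by Schoenfeld, which the 34–38 expected without dropout would meet, but the 27–31 left after 20% loss would not.

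*The source of the 100 s is inferred.* The protocol does not say outright that it rests on the single patient scan; that is only the one conventional pilot scan described. The simulator and the single patient are already disclosed, so asking for that disclosure again adds little.

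*The gap is small.* Before dropout it is about 2 to 6 points. With the protocol's own dropout it is about 9 to 14.

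**Conclusion.** The point stands, conditional on HR 2.78 and a two-sided 5% test. The 90% claim requires about 41 events, while the cap and the censoring rule make events fewer than scans. The dropout arithmetic is wrong whatever is assumed: 46 covers about 9% loss, not 20%. After a 20% loss, power cannot exceed about 87%. Under exponential times, 46 scans give about 76–88%, depending on dropout and on whether the pilot times are medians or means, before wrong diagnoses and clustering.

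The HR of 2.78 is a weak planning value: it is a ratio of times that appears to set simulator scans against one scan in a patient. That does not show the true effect is smaller. Nor does any of this make the Cox analysis invalid or oblige the trial to recruit more; it shows that the printed power is not what the design delivers at its own planning value.

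**What to change.** Rewrite the Sample size paragraph to:

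1. State the requirement as about 41 events (correct diagnoses within 120 s) for HR 2.78, two-sided 5%, 90% power, and name the gsDesign function and settings used.
2. State the assumed proportion of scans with a correct diagnosis by 120 s in each arm, and say whether 36 s and 100 s are means or medians.
3. Correct the dropout statement: 46 scans allow about 9% loss from 42, and a 20% allowance would be 53.
4. Replace the 90% claim with the power that 46 scans give at HR 2.78: about 76–88% on the assumptions above, before clustering by operator.

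Power at a smaller hazard ratio, such as 2.0, would be a useful but secondary addition given the thin pilot basis.

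The cost is one rewritten paragraph and a less favourable stated power. No added scans are needed, and conduct and analysis are unchanged. For scale only, 41 expected events would take about 50–56 evaluable scans under the step 4 assumptions.

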**Methods:**

This is a single-center and randomized controlled trial which will be implemented in Peking Union Medical College Hospital, Beijing, China. A total of 46 TEE scans are schemed to be performed by 6 operators participating in and randomly assigned to either the PReTEE or the conventional TEE group. This study is purposed to investigate whether the efficiency of discriminating leading causes of difficult CPB wean-off can be significantly improved via an abbreviated sequence of TEE views. The primary outcome of interest is the difference between the groups of PReTEE and the conventional TEE in the successful discrimination of etiologies in specified 120 s. Cox proportional hazards model will be further employed to calculate the outcome difference.

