### *Trial design* {8}

This is a single-center and randomized controlled trial which will be prospectively conducted at Peking Union Medical College Hospital, Beijing, China. The six TEE operators participating in this trial will be randomly assigned in a 1:1 fashion into the PReTEE group and the conventional TEE group. This protocol strictly conforms to the Standard Protocol Items Recommendation for Interventional Trials (SPIRIT) Checklist (Table 1).

**Table 1 Tab1:** SPIRIT flow diagram. *PReTEE* perioperative rescue transesophageal echocardiography, *TEE* transesophageal echocardiography

	**Enrolment**	**Allocation**	**Post-allocation**	
Timepoint**	**Pre-allocation** **-t**_**1**_	**Preoperative** **0**	**Procedure** **t**_**1**_	***t***_***2***_
Enrolment:				
Eligibility screen	X			
Informed consent	X			
Allocation		X		
Interventions:				
PReTEE			X	X
Conventional TEE			X	X
Assessments:				
Outcome measurements			X	X
Adverse event evaluation			X	X

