### Methods in analysis to handle protocol non-adherence and any statistical methods to handle missing data {20c}

The loss regarding the times of TEE scan by operators in each cardiac surgical procedure will be controlled by adhering to the trial methods depicted above. We suppose that the number of missing data would be relatively limited. The dropout rate of 20% is also accounted for when calculating the sample size.

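### A 20% dropout allowance on 42 scans gives 53, not 46; the planned 46 retains 42 scans only up to 8.7% loss

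*Protocol article*

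**What the plan says.** All the figures are in the protocol article; no separate analysis plan is shown.

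- **Sample size {14}** gives preliminary times: "the time of finding out the cardiac etiologies in the PReTEE group was 36 s, whereas in the conventional group was 100 s". It sets 90% power at a 5% significance level and states that "42 TEE examinations should be conducted among eligible patients", "using a hazard ratio of 2.78". The next sentence reads: "Considering a 20% dropout rate, a total of 46 TEEs are schemed to be consecutively performed".
- **Abstract, Methods** repeats the total: "A total of 46 TEE scans are schemed to be performed by 6 operators".
- **Methods in analysis to handle protocol non-adherence and any statistical methods to handle missing data {20c}** says that losses will be controlled by following the trial methods and that little missing data is expected. It adds: "The dropout rate of 20% is also accounted for when calculating the sample size".

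The article gives no other dropout rate and no other route from 42 to 46.

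**The concern.** The base (42), the loss rate (20%) and the total (46) are all stated, and the total does not follow from the other two. The increase is 4 scans on 42, or 9.5%, which is about half of what the shortest form of a 20% allowance would add.

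Two things depend on it. The trial's headline sample size rests on a justification that does not produce it. And {20c}, which names no analytic method for missing data, cites this allowance as part of its provision. A reader would conclude that one scan in five could be lost with the stated power intact. On the plan's own figures that is not so.

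**Working it through.** **Inputs.** Hazard ratio 2.78, power 90%, significance level 5%, base 42, dropout 20% and total 46, all from {14}. The 1:1 ratio is from Trial design {8}, where it applies to operators; I take it for scans too. Sidedness is not stated; I take two-sided and also try one-sided.

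**Step 1: reproduce the base.** The hazard ratio is the ratio of the preliminary times: 100/36 = 2.78. Schoenfeld's formula for 1:1 allocation:

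- d = 4 × (1.960 + 1.282)² / (ln 2.78)² = 40.2, so 41, or 42 when made even for two arms.

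The stated 42 is therefore reproduced as a two-sided Schoenfeld figure.

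**Step 2: apply the 20% allowance.**

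| Base | n/(1 − 0.20) | n × 1.20 |
|---|---|---|
| 42 (stated) | 52.5 → 53 | 50.4 → 51 |
| 41 | 51.25 → 52 | 49.2 → 50 |
| 40.2 (unrounded) | 50.3 → 51 | 48.2 → 49 |

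None gives 46. Other event formulas do not help, because they do not start from 42:

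- One-sided Schoenfeld gives 33, which becomes 42 or 40.
- Two-sided Freedman gives 48, already above 46.
- One-sided Freedman gives 39. Here 39 × 1.2 = 46.8 (47) comes close to the total, but its base contradicts the stated 42.

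**Step 3: find the loss that 46 does cover.**

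- To retain 42 scans: 1 − 42/46 = 8.7%.
- An allowance of about 10% fits the total: 42 × 1.10 = 46.2.

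**Step 4: power if 20% is lost.** Scans left: 46 × 0.8 = 36.8. Treating every scan as an event, as the plan's use of 42 does:

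- Power = Φ(√(36.8/4) × ln 2.78 − 1.96) = Φ(3.033 × 1.0225 − 1.96) = Φ(1.141) = 87.3%.

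| Events | Power |
|---|---|
| 36 | 86.6% |
| 37 | 87.5% |
| 42 | 91.2% |
| 46 (no loss) | 93.4% |
| 53 | 96.1% |

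**Side calculation, resting on an assumption.** Statistical methods {20a} censors failed diagnoses, so not every scan is an event. Suppose exponential times, with 36 s and 100 s read as medians or as means, and the 120 s limit. Then about 73% to 83% of scans would be events. The 36.8 remaining scans would yield 27.0 to 30.6 events, with power of 76% to 81%. The article does not give that distribution, and the difference between events and scans is a separate matter. The finding does not need this range.

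**The case against.** Four points can be made for the plan.

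1. **The power loss is conditional.** With no loss, 46 scans give 93.4% on the plan's own basis, and at exactly 20% loss the shortfall from 90% is about 3 points. This stands. The outcome is one scan of at most 120 s, and {20c} expects little missing data. But scans can be halted and patients can withdraw, and it is the protocol that names 20% and says it is covered.

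2. **The 8.7% is measured against the rounded 42.** This also stands. Against the unrounded requirement, 90% power survives a loss of 1 − 40.2/46 = 12.6%, or 10.9% against 41 events. The 8.7% is the loss at which the plan's own stated requirement of 42 scans is no longer met. On either measure, 20% is not covered.

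3. **The software may have treated dropout as a hazard, not as a fraction of scans.** {14} names the gsDesign package. If 0.20 per 120 s was entered as an exponential loss hazard with no time limit (an assumption), some settings land near 46. A one-sided rate-difference form with the times as means goes from 42.3 to 45.7; a two-sided log-hazard form with the times as medians goes from 40.3 to 46.0. This offers a possible origin for the number but does not rescue the text. The article states no such hazard, most settings do not give 46, and these ignore the 120 s limit. Nor would 20% of scans then be lost. In the first setting the fractions observed to diagnosis are (1/36)/(1/36 + 0.2/120) = 0.943 and (1/100)/(1/100 + 0.2/120) = 0.857. Their mean is 0.900, so the loss allowed for is about 10%.

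4. **The remedy can be wording alone.** True, and that makes it cheap. It does not make the stated figure right.

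**Conclusion.** The concern holds. A base of 42 with a 20% allowance requires 53 scans (51 by the shortcut), and the planned 46 keeps 42 scans only up to 8.7% loss. This part is arithmetic on the protocol's own figures and needs no assumption.

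The effect on power is real but conditional. If 20% of scans were lost, about 37 would remain and power would be about 87% instead of 90%. That assumes two-sided 5%, equal arms and an event in every remaining scan. It is the favourable case, since failed diagnoses are to be censored.

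**What to change.** Choose one of the following and make the abstract, {14} and {20c} agree.

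- **Keep 46 and correct the allowance:** say that 46 scans retain the required 42 with up to about 9% loss. Replace the 20% in {20c} to match.
- **Keep 46 and keep 20%:** state that this leaves about 37 evaluable scans and restate the power there, about 87% if every scan is counted as an event.
- **Keep 20% and the requirement of 42:** raise the total to 53, or 54 for equal arms.

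The first two change wording only, at the price of a less favourable figure. The third adds 7 or 8 scans and is a sample-size amendment, which under the section on protocol amendments {25} goes to the ethics committee. If the 46 came from a hazard-type dropout setting in the software, {14} should say so and give the inputs, and should not describe it as a 20% allowance.
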